### Sample size

There are currently 6518 students enrolled in the 10^th^ and 11^th^ grades in State-financed schools in the commune of Santiago. Using a 99% confidence level and a 5% error margin, the sample framework is 605 students, which will be divided into the study and control groups. The statistical power is determined using an analysis of variance with a significance level of 0.05, a sample size of 605 and an expected difference of 0.2 points between groups, which will provide a statistical power of at least 0.8. The 0.2 difference is the smallest reported in previous studies comparing the scores of two groups with the instruments that will be used; it was reported in the analysis of the scores of the scale of ambivalent sexism [24].

The statistical power was calculated using the software G*Power [25]. After making a slight adjustment due to the number of students currently enrolled in each school at each level, the definitive size of the experimental phase of the study will be 609 students.

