### Outcomes

Before implementing the workshop, we will perform a base-level measurement of the variables in the students. Later we will measure the result variables in two moments, just after the workshop closes and 3 months after the closure, in order to evaluate the results obtained by the intervention, to determine the effect of the program.

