### Analytical methods

The information that results from the application of the scales will be summarized with descriptive statistics (frequency table, mean, standard error, and asymmetry coefficient) for the pre- and post-intervention evaluations.

Since the intervention has specific objectives for each session, it is not appropriate to impute missing data. However, to account for the potential lack of adherence by some students, it is suggested that participants who miss more than 30% of the sessions should not be included in the data analysis. Regardless of attendance, students will be able to participate in all workshop activities.

We will compare the three evaluations, incorporating information relative to the type of school and course. If the data are normally distributed, we will perform one-way ANOVAs, incorporating post hoc information of the results when necessary, and perform pair-wise comparisons using the Tukey or Games-Howell test.

After the variables with main effects are established, we will perform a factorial ANOVA, in which one of the factors will be fixed (i.e., type of school) and the other will be the repeated measures of the three evaluations. As well as evaluating if the main effects are sustained over time, this will evaluate possible interactions among the studied factors. In this case, following the guidelines proposed by Cohen^75^ for ANOVAs with two or more factors, the effect size will be reported as the partial Eta^2^ statistic. The interpretation of the effect sizes will consider the suggestions of Cohen [50]. These analyses will use the program Jamovi version 1.2 [51].

No interim data analysis will be conducted, and there will be no stopping guidelines.

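### The three-time-point factorial ANOVA is given the question of sustained effects, but its omnibus F and partial Eta² do not separate an effect kept at 3 months from one that has vanished

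*Protocol article*

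**What the plan says.** The Outcomes section sets a baseline and two later measurements, "just after the workshop closes and 3 months after the closure". Analytical methods then describes two steps.

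- **First step.** The three evaluations are compared by one-way ANOVAs, "incorporating post hoc information of the results when necessary, and perform pair-wise comparisons using the Tukey or Games-Howell test". The factor of these ANOVAs is not named.
- **Second step.** For variables that show main effects, a factorial ANOVA follows, in which "one of the factors will be fixed (i.e., type of school) and the other will be the repeated measures of the three evaluations". The durability question is given to this model: "As well as evaluating if the main effects are sustained over time, this will evaluate possible interactions among the studied factors". Its effect size is to be partial Eta².

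The factorial paragraph names no study-minus-control contrast at 3 months and no rule for deciding that an effect is sustained. The descriptive summaries in the same section are specified for the pre- and post-intervention evaluations only.

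**The concern.** The 3-month visit is one of only two outcome times, and its particular use is to show whether any benefit lasts. A durability claim needs evidence about what is left at 3 months, or about how much was lost after the programme ended. The omnibus test of a three-level repeated factor has a different null hypothesis: that all three means, or all three between-group differences, are equal. A rise that returns to its starting level breaks that null as surely as a rise that holds. A programme whose effect had gone by 3 months could therefore give a significant F and a respectable partial Eta² in the very analysis that the article presents as the check on durability.

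**Working it through.** **Inputs from the article.** 301 study and 308 control students (Table 1). Sample size gives "with a significance level of 0.05, a sample size of 605 and an expected difference of 0.2 points between groups".

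**Assumptions.** The article gives no SD, so SD = 1 and d = 0.2. It gives no within-student correlation r and no school ICC, so ranges are shown. Study arm is placed in the model as the between-student factor, although the article names type of school. Clustering is ignored until step 5.

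**The plan's own figure.** None is given for the factorial ANOVA. The sample size does reproduce. N z²pq / [e²(N − 1) + z²pq] with N = 6518, p = 0.5 and e = 0.05 gives 603 with z = 2.576 and 605 with z = 2.58, against the stated 605.

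**1. Size of the departure from the null.** Write the arm difference at baseline, post and 3 months as a profile.
- Kept (0, d, d): mean 2d/3; sum of squares 4d²/9 + d²/9 + d²/9 = 0.667d².
- Vanished (0, d, 0): mean d/3; sum of squares d²/9 + 4d²/9 + d²/9 = 0.667d².

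The two are identical.

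**2. Group-by-time F, equal correlations.** λ = [n₁n₂/(n₁ + n₂)] × 0.667d² / (1 − r), with n₁n₂/(n₁ + n₂) = 301 × 308 / 609 = 152.2 and 2 and 1,214 df.

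| r | λ | Rejects if kept | Rejects if vanished |
|---|---|---|---|
| 0.5 | 8.12 | 72% | 72% |
| 0.6 | 10.15 | 82% | 82% |
| 0.7 | 13.53 | 92% | 92% |

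The distribution of partial Eta² is also the same in the two cases. Simulation at r = 0.5 gave 73.3% (kept) and 73.0% (vanished).

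**3. Unequal correlations** (simulated, 3,000 trials each).
- AR(1) with 0.7: 82.1% kept, 91.1% vanished (80.3% and 89.4% with the Greenhouse-Geisser correction).
- Correlations 0.6, 0.5 and 0.7 for baseline–post, baseline–3 months and post–3 months: 79.9% kept, 86.3% vanished (78.9% and 85.0% corrected).

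In both scenarios the vanished effect is detected more often.

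**4. Other tests, d = 0.2.**
- *Between-student main effect.* It averages the three times, so it sees 2d/3 if kept and d/3 if vanished, with variance (1 + 2r)/3. At r = 0.5, λ = 152.2 × 0.0178 / 0.667 = 4.06 and 152.2 × 0.00444 / 0.667 = 1.01, so it rejects 52% versus 17%. It separates the cases in part, yet still fires well above 5% when nothing is left.
- *Arm contrast on the change from baseline to 3 months.* λ = 152.2 × 0.04 / [2(1 − r)] = 7.61 at r = 0.6, so it rejects 79% if kept and 5% if vanished.

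**5. The contrast with schools as the unit.** 5 versus 5 schools of 609/10 = 60.9 students, noncentral t on 8 df, r = 0.6. The variance is 2(1 − 0.6) = 0.8 for change, or 1 − 0.6² = 0.64 with baseline adjustment. SE = √[2 × variance × (1 + 59.9 × ICC) / 304.5].

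| Assumed ICC | SE, change | Power, change | Power, baseline-adjusted |
|---|---|---|---|
| 0 | 0.072 | 68% | 77% |
| 0.02 | 0.107 | 37% | 45% |
| 0.05 | 0.145 | 23% | 28% |

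**The case against.** The strongest reply is that a factorial repeated-measures ANOVA is a model, not a single F. It also yields means by time and follow-up contrasts, and a condensed article may leave those to the full plan. Much of this stands, and it rules out three stronger readings.

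- *A reader might infer that a significant omnibus F will be declared proof of a sustained effect.* The article states no such rule. It also does not propose reading a non-significant post versus 3-month pair as persistence.
- *A reader might infer that nothing in the plan can show durability.* The one-way step is ambiguous. Tukey and Games-Howell are between-group procedures, and one plausible reading is a group comparison at each evaluation, including 3 months. However, those tests are described in the earlier step and are not tied to the question of sustained effects.
- *A reader might infer that the F always rejects equally often.* Exact equality needs equal correlations, and the between-student main effect does separate the cases in part.

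It is also fair that the figures insert study arm where the article names type of school. If arm is truly absent, that is the more basic defect; adding it does not cure this one. What the reply does not remove is that the article goes beyond silence: it assigns a question to a named analysis and effect size whose omnibus test does not answer it.

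**Conclusion.** The point holds in limited form. The omnibus F for time or group by time, with its partial Eta², is not evidence on whether an effect lasts to 3 months. With equal correlations its rejection rate is the same for a kept and a vanished 0.2 SD effect; in the two unequal-correlation scenarios tried, it favoured the vanished effect by about 6 and 9 percentage points before correction. The identity of the two sums of squares needs no assumption about SD or correlation. The percentages rest on SD = 1, the assumed correlations, arm in the model and no clustering. The fault lies in the stated purpose of the test. The documents do not show that a false durability claim will follow.

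**What to change.** Replace the sentence on sustained effects with two named contrasts, estimated from the same model as the main comparison and with school clustering accounted for:

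1. The study-minus-control difference at 3 months, adjusted for baseline, with its 95% CI. This is the basis for any claim that an effect remains at 3 months. An interval that excludes zero shows that some effect remains, not that all of it does.
2. The study-minus-control difference in change from post-intervention to 3 months, with its 95% CI, as the estimate of decay.

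State that the omnibus F alone is not evidence of a sustained effect. A non-significant second contrast should not be read as persistence either: by the school-level calculation, which has the same variance for this change, complete loss of a 0.2 SD effect would be missed 100 − 68 = 32% of the time at ICC 0 and 100 − 23 = 77% at ICC 0.05.

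The cost is one paragraph, with no new data and no extra students. The downside is lower power for the durability claim. The 79% for the simple change contrast ignores clustering; with 5 versus 5 schools it becomes about 68%, 37% and 23% at assumed ICCs of 0, 0.02 and 0.05, or 77%, 45% and 28% with baseline adjustment.

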### Ethics

This study implies a minimum risk for the adolescents, with the possibility of a direct benefit, since the probability and magnitude of damage and the discomfort possible to be foreseen in the research are no greater than those found commonly in the daily life or during physical or routine psychological tests [46]. We will establish confidentially in the application of the instruments and the presentation of the results. This will be recorded and signed both in the informed consent of the adolescents and in that of the parents or legally responsible adults. Participants will have the option of withdrawing from the study at any moment; they will be informed of its purpose and the way the results will be used. The authors will meet every 2 weeks to supervise the application of the study and the clinical and research integrity. If modifications need to be made to the protocol, the study committee will notify the Municipality of Santiago, the participants, and update the trial registry.

Results of the trial will be submitted for publication in peer-reviewed journals and findings will be presented at scientific conferences and to key service providers and policymakers. The study was approved by the Ethics Committee of the Faculty of Social Sciences of the Universidad de Chile, the institution to which the principal and corresponding researcher belongs. The committee will monitor and safeguard the data.

## Discussion

Sexual and reproductive health are relational processes of construction in which the social context and individual, family, and community behavior intervene. Because of this, world organizations recommend an integrated focus of promotion of sexual health, with effective participation of all sectors of the society and the combination of complementary multi-sector strategies, to ensure informed and healthy populations by the application of interventions that promote safe sexual behavior [47]. This is especially sensitive in adolescence, since this stage is the opportune moment to develop healthy habits and lifestyles related to sexual health.

This stage is a period of emotional and social change, in which adolescents begin to explore sexuality and relate actively to others. In fact, an important proportion is sexually active, and this proportion increases in late adolescence [3]. Thus education in sexual and reproductive health during this stage of the life cycle is key, since the information and knowledge are central to self-care and the incorporation of preventive measures in the exercise of sexuality [47]. Thus initiatives are required to evaluate the design and implementation of interventions and/or programs that contribute to improve the health of this population in this ambit.

This study presents the study protocol of an GRTs study of an intervention in the sexual health of Chilean adolescents, centered mainly on evaluating the effectiveness of an intervention with a comprehensive and gender-transforming perspective. Given the responsibility of public health in adolescent sexual and reproductive health, the provision of resources and options to educate in an integral, scientific manner with a contextualized gender focus becomes an imperious need.

The development of interventions on this topic is urgent, given the magnitude of non-intended adolescent pregnancy, the high rates of STI in the adolescent and young adult population (which represent 55% of the cases notified in the last 10 years) and the progressive growth in the HIV notification rate in adolescents. The prevalence of risky sexual behavior shows that the increase in self-care measures has been unequal in men and women [47]. Adolescents have reported that the information they receive from schools, health professionals, and their families is insufficient, thus they turn to friends, television, and the Internet, in spite of knowing the limitations of these sources [52].

Thus interventions are required that offer friendly, quality spaces for adolescents, with emphasis on sexual and reproductive health, ensuring sexual education in the education structure and incorporating the family and community as socializing and protective agents [47]. Women, men, and persons of sexual diversity should have the same opportunities to accede to life conditions and services to maintain good health, without becoming ill, incapacitated, or dying for avoidable causes [47].

The innovative aspects of the proposal should be highlighted. This study is proposed based on Implementation Science, a relatively recent framework of study on the processes to be put in practice to make effective an evidence-based intervention in a new context [53], whose results will serve as necessary preconditions to produce changes, since they will indicate what is or is not successful in the execution of an intervention [54]. The proposal also contributes to fill a gap in this aspect, since there are few public reports on the implementation of interventions in schools, particularly in sexual health [55].

Another innovative aspect is the use of Gender-Based Analysis, a recent practice in health research [56] and in implementation studies [48]. This kind of analysis implies an analytical process that examines how gender impacts the effectiveness of the interventions, considering social norms and economic and cultural conditions and evaluating how and why different subpopulations (e.g., groups considering their gender, age or socioeconomic status) experiment certain conditions of health and interventions [21].

## Trial status

This study was registered on June 6, 2023, at ClinicalTrials.gov ID: NCT05896540. Recruitment will begin in September 2023 and end in July 2024. Protocol version number 1.0. May 22, 2023.

## Data Availability

The data that will be generated and analyzed during the current study will be available from the corresponding author upon reasonable request.
